## Abstract

Abdominal surgeries make up a significant portion of all surgical procedures performed worldwide. Despite advances in surgical techniques, there is significant morbidity and mortality associated with abdominal surgeries. Cardiopulmonary complications in the postoperative period play an important part in the elevated risk associated with these surgeries. Preoperative medical assessments have therefore become the standard of care to evaluate the risk of surgery, optimize a patient's medical conditions, and mitigate the perioperative risk. While there has been increasing utilization of lung point of care ultrasound (POCUS) in the immediate preoperative setting, the use of lung POCUS at the preoperative medical assessment clinic visit has not been studied. While using risk stratification tools is common in current practice, the role of adjunctive office-based techniques like lung POCUS have not been studied in this setting. We conducted an observational prospective pilot study to evaluate the association of lung POCUS findings in the preoperative visit on the risk of adverse cardiopulmonary outcomes in the 30-day postoperative period after major abdominal surgery. A standardized scoring system called integrated lung ultrasound score (iLUS) is used for objective assessment. Our study attempted to determine whether the addition of lung POCUS can be used to better stratify the risk for postoperative complications.

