Cardiovascular complications, mainly myocardial ischemia, left ventricular dysfunction, and arrhythmia—occur in one in seven patients older than 45 years within 30 days from an inpatient non-cardiac surgery [6]. Similarly, pulmonary complications are common—particularly after major abdominal surgery—with an estimated incidence of 9 to 40%. Atelectasis, pneumonia, and pulmonary aspiration are among the most common postoperative complications and can impact survival after surgery. Preoperative medical assessment prior to every major surgery has become the standard of care with objectives to assess the perioperative risk for morbidity and mortality, optimize the patient's medical condition, and mitigate the risk for cardiopulmonary complications and others [9]. A number of validated risk stratification tools, such as the Revised Cardiac Risk Index (RCRI), American University of Beirut (AUB)-HAS2 Cardiovascular Risk Index, the American Society of Anesthesiologist's Physical Status (ASA-PS), and the Gupta perioperative risk for myocardial infarction and cardiac arrest have been created and used to standardize and optimize the perioperative medical assessment process [10–12]. The utilization of point of care ultrasound (POCUS)—the application of portable ultrasound by clinicians at the bedside—has grown rapidly in the inpatient and outpatient settings and is a valuable tool that enhances the standard clinical assessment [13]. In particular, lung POCUS can reveal findings, such as mild pulmonary edema, atelectasis, fibrosis, or small pleural effusions, which can be subclinical and otherwise not detected by history and physical examination alone [14]. A structured approach to performing and evaluating lung POCUS has been highly useful. This was originally known as the lung ultrasound score, and was later refined by Dell'Aquila et al. as the integrated lung ultrasound score (iLUS) [15,16].

Studies conducted in the immediate preoperative period have shown that lung POCUS performed during anesthesiology evaluation can aid in determining fluid therapy and predicting major adverse cardiac events [17,18]. However, the specific role of POCUS beyond this immediate preoperative assessment of patients has not been studied adequately, especially in the clinic setting at the time of preoperative medical assessment [19].

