## Aims and Hypothesis

We aim to study the value of adjunctive iLUS at the time of preoperative medical assessment by internal medicine physicians on postoperative cardiopulmonary outcomes. Our primary hypothesis is that early lung POCUS assessment in moderate- to high-risk adult patients over 50-years-old undergoing abdominal surgery can reduce postoperative complications, thereby decreasing intensive care unit admissions, mortality, hospital length of stay, and readmissions.

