### Methodology of Analysis

The following 3 classifications of patients will be performed based on the iLUS: i) iLUS 0 vs. >0, ii) iLUS < mean iLUS vs. ≥ mean iLUS, iii) iLUS < median iLUS vs. ≥ median iLUS.

Continuous variables will be presented as mean with standard deviation and median with interquartile range. Categorical variables will be presented in absolute and relative frequencies. The appropriate parametric and non-parametric tests will be utilized for generating comparisons.

A sensitivity analysis will be performed for patients enrolled in the Jacobi site and patients enrolled in the Laikon site. Sensitivity analyses will be performed for various patient groups based on RCRI, ASA-PS, and AUB-HAS-2 scores, as well as whether the surgery was emergent or elective as deemed by the primary surgical team [23].

Multivariate analysis will be performed including iLUS classification and the following variables: age, sex, body mass index (BMI), RCRI, ASA-PS, and AUB-HAS-2 scores, time from POCUS scan to surgery, and emergent vs. elective surgery.

In addition, to preserve the integrity of our analysis while still reporting critical lung POCUS results, we will implement the following analysis: All patients enrolled in the study will be included in the primary analysis based on the intention-to-treat (ITT) principle to ensure that our results will reflect real-world practices. Patients with critical POCUS findings prompting interventions, postponement, or cancellation of surgery will be retained in the ITT analysis to maintain randomization integrity. Additionally, a pre-specified subgroup analysis will focus exclusively on these patients to evaluate the specific impact of the critical POCUS results on outcomes such as completion of surgery, postoperative complications, intensive care unit admission, mortality, length of stay, and readmissions. To further assess the robustness of our findings, a sensitivity analysis will be conducted, excluding patients with critical findings to evaluate the effect of blinding on the study outcomes.

An interim analysis will be performed after the follow-up completion of 60 participants (with at least 10 participants at the Laikon site). Should the interim analysis reveal findings that decisively confirm or reject the study hypothesis, no more participants will be enrolled, and the study will be ended after the follow-up completion of the last enrolled participant.

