## Discussion

There is an emerging role of POCUS in the perioperative setting with its use by anesthesiologists in operative rooms for regional anesthesia and line insertion [24]. The use of cardiac POCUS in the preoperative evaluation of patients with femur neck fracture repair was found to show a significant decrease in both 30-day and 1-year mortality [25]. A similar demonstration of the utility and feasibility of preoperative-focused ultrasound was demonstrated by Cowie, however, most of the assessments occurred immediately prior to surgery [26]. This increasing use of perioperative POCUS is well-established among anesthesiologists in other contexts as well, such as in the setting of difficult laryngoscopies and for assessment of intra-abdominal fluid extravasation after hip surgery [27]. However, the utilization of lung POCUS in the preoperative medical setting is limited, as well as the respective research. Incorporating early lung POCUS into preoperative medical assessments will provide valuable additional context for optimizing both pre- and perioperative care. This approach may guide medication adjustments, potential postponement, or cancellation of surgery based on findings, enabling internal medicine physicians to offer more informed recommendations to surgical and anesthesia colleagues regarding medical risks.

Current guidelines only recommend adjunctive workup with electrocardiogram and echocardiograms in patients who have specific risk factors [28]. The scope of POCUS as an adjunctive assessment tool for cardiac or lung dysfunction has not been described in preoperative guidelines [29]. While there are studies evaluating the impact of lung POCUS examination by anesthesiologists in the perioperative period, the impact of lung POCUS by internal medicine specialists at the time of preoperative medical assessments has not been well described [30]. Therefore, this pilot study was designed to evaluate the possible role of lung POCUS in preoperative medical evaluation and the possible association of its findings with postoperative cardiopulmonary outcomes.

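### The planned model can test whether a dichotomised iLUS adds information to the existing risk scores, but nothing in the plan measures how much it improves risk stratification

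*Protocol article*

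**What the plan says.** The protocol article describes its purpose in several ways.

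- **Association.** The Abstract says the study is "to evaluate the association of lung POCUS findings in the preoperative visit on the risk of adverse cardiopulmonary outcomes", and the Discussion repeats this as "the possible association of its findings with postoperative cardiopulmonary outcomes".
- **Added value.** The Abstract closes by asking "whether the addition of lung POCUS can be used to better stratify the risk for postoperative complications". Aims and Hypothesis takes the same line: "We aim to study the value of adjunctive iLUS at the time of preoperative medical assessment".
- **Effect on outcomes.** The primary hypothesis in Aims and Hypothesis is that early POCUS "can reduce postoperative complications, thereby decreasing intensive care unit admissions, mortality, hospital length of stay, and readmissions". That is a separate matter and is not pursued here.

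The Introduction names the risk tools already in use: RCRI, AUB-HAS2, ASA-PS and the Gupta index.

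Under Intervention, iLUS is a score from 0 to 40. Methodology of Analysis uses it only as three two-group splits: "iLUS 0 vs. >0, ii) iLUS < mean iLUS vs. ≥ mean iLUS, iii) iLUS < median iLUS vs. ≥ median iLUS". It then plans group comparisons, analyses in patient groups defined by RCRI, ASA-PS and AUB-HAS-2, and one adjusted model: "Multivariate analysis will be performed including iLUS classification and the following variables: age, sex, body mass index (BMI), RCRI, ASA-PS, and AUB-HAS-2 scores", plus time from scan to surgery and emergent versus elective surgery. Significance is judged at p ≤0.05. The section gives no comparison of models with and without iLUS, and no analysis of iLUS as a continuous score.

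**The concern.** Asking whether an added test stratifies risk better is a question about increment: how much better are patients ranked or grouped once iLUS joins what the clinician already has? An adjusted odds ratio for an iLUS group answers a different question, namely whether the group is associated with outcome at fixed values of the other covariates. A marker can pass that test and barely change the ranking of patients.

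If the analysis is run as written, a significant iLUS term would be the only adjusted evidence available on the second aim, and it could be read as showing better stratification. The Conclusion says the results are meant to inform larger randomised trials, so an overstated claim would carry forward. The splits also discard information in a study of 120 patients that has little to spare.

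**Working it through.** The plan gives no effect size, C-statistic or power on this point, so there is no figure to reproduce. The checks below are illustrative.

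**1. Aim against analysis.**

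| Stated purpose | Planned analysis that bears on it | Match |
|---|---|---|
| Association with 30-day outcomes | Group comparisons, analyses by score group, adjusted model | Yes |
| Better stratification by adding POCUS | Adjusted iLUS term; analyses within score groups | Tests for added information; gives no size of gain |

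**2. From odds ratio to gain in C.**

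Assumptions:
- a standard normal base score x with nominal C of 0.65, 0.70 or 0.75 and coefficient s = √2·Φ⁻¹(C)
- an independent two-group marker b with 50% prevalence and coefficient ln(OR)
- an intercept set to give event rates of 10%, 20% or 40%, a range prompted by the background figures in the Introduction (6.7% to 13.8% for 30-day morbidity, 9% to 40% for pulmonary complications), since no rate is given for the composite

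The simulation used 400,000 patients per setting. The gain is C(s·x + ln(OR)·b) minus C(x). The three entries per cell are for event rates of 10%, 20% and 40%.

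| Nominal base C | OR 2 | OR 3 | OR 4 |
|---|---|---|---|
| 0.65 | 0.025, 0.028, 0.028 | 0.058, 0.062, 0.064 | 0.084, 0.086, 0.093 |
| 0.70 | 0.020, 0.020, 0.020 | 0.043, 0.045, 0.048 | 0.062, 0.069, 0.073 |
| 0.75 | 0.014, 0.015, 0.015 | 0.033, 0.035, 0.038 | 0.049, 0.054, 0.056 |

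Example: at nominal C 0.70, 10% events and OR 2, the gain is 0.714 − 0.694 = 0.020. The realised base C was a little below nominal (here 0.694). For a given odds ratio the gain varies by up to about a factor of two with the strength of the base score (OR 2: 0.014 to 0.028). It therefore has to be estimated and cannot be read off the odds ratio.

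**3. Cost of the splits.** For a normally distributed marker, the relative efficiency of a median split is 2/π = 0.637, so 120 patients carry the information of 120 × 0.637 = 76. At n = 120, with an assumed log odds ratio of 0.5 per SD and one base score (600 runs per setting):

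| Intended event rate | Power, continuous | Power, median split |
|---|---|---|
| about 10% | 36% | 26% |
| about 20% | 59% | 39% |
| about 40% | 68% | 48% |

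**4. How large a base model the data allow.** The planned model has iLUS plus eight covariates, or nine terms at one degree of freedom each. Events per term are 120 × rate / 9:
- 6.7%: 8.0 events, 0.9 per term
- 9%: 10.8 events, 1.2 per term
- 13.8%: 16.6 events, 1.8 per term
- 40%: 48 events, 5.3 per term

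**5. Optimism.** In the step 3 runs at about 10% events, the apparent gain in C from the median split averaged 0.04 over all runs, but 0.09 in the runs where the split was significant. An uncorrected gain reported alongside a significant result would be inflated.

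**The case against.** A reader might infer that the plan **cannot answer** the stratification question at all. That goes too far. RCRI, ASA-PS and AUB-HAS-2 are covariates, so the iLUS term does test for prognostic information beyond them. For a one-degree-of-freedom term, a likelihood-ratio comparison of models with and without it addresses the same null hypothesis. The analyses within score groups also bear on the question. What is missing is the size of the gain.

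A reader might also infer that the aim is to **outperform the existing indices**. The Abstract speaks of adding POCUS and names no index in that sentence. Added value over the tools in the Introduction is a fair reading; superiority to them is not. Association is also a stated purpose, and the analysis matches it.

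A third tempting step is to set the gain against the **standard error of a single C-statistic**. The two C-statistics come from the same patients and are correlated. In simulation at n = 120, 10% to 15% events and OR 2, the SD of the change was 0.031 to 0.038, against 0.068 to 0.080 for C itself. A gain of 0.02 would still be hard to demonstrate, but the standard error of a single C overstates the imprecision by about a factor of two.

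Finally, performance metrics are often left to a SAP, and this is a condensed account of a pilot. Their absence alone would be no finding. But the article does fix the form of iLUS, the covariates and the threshold, and a SAP that followed it would inherit both the dichotomy and the mismatch with the second aim. It also stands that 120 patients will not settle the size of the gain, which is why the added analysis should be exploratory.

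**Conclusion.** The concern holds in a limited form. The analysis fits the association aim. For the added-value aim it can test whether a dichotomised iLUS carries information beyond the existing scores, but it does not quantify any improvement in stratification, and the splits weaken even that test. An adjusted odds ratio of 2 corresponds to a gain in C of about 0.01 to 0.03, and one of 3 to about 0.03 to 0.06.

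These sizes rest on assumed base C-statistics, event rates, an even split and an iLUS independent of the base score. The 64% figure assumes a normally distributed marker, and the documents do not give the distribution of iLUS. The mismatch between aim and analysis does not depend on any of these figures.

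**What to change.** In Methodology of Analysis, specify the added-value analysis as a nested comparison:

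- a small base model of the existing clinical indices, limited to what the number of events supports;
- the same model with iLUS added as one continuous term;
- the likelihood-ratio test, and the optimism-corrected change in C with a bootstrap interval for the paired difference;
- a label of exploratory.

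Rest any statement about better stratification on this comparison and not on the adjusted odds ratio. The alternative is to limit the aim in the Abstract to association, in which case the nested comparison is not needed for the stated purpose.

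The cost is a few lines of analysis on data already being collected. The price in reporting is that the estimated gain will probably be small and imprecise, and will look less favourable than an odds ratio.

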## Introduction

Each year, more than 300 million patients receive a major surgery worldwide; around 50 million in the Unites States and 20 million in Europe [1–3]. Abdominal surgeries consist of about 15% of all surgeries [4]. Despite the tremendous advances and overall outcome improvement in surgery, the perioperative morbidity and mortality remain significant. A study based on the American College of Surgeons National Surgery Quality Improvement Program database estimated 30-day postoperative mortality rates by surgical urgency: 0.4% for elective procedures, 2.3% for urgent surgeries, and 3.7% for emergent cases. In contrast, 30-day morbidity rates were remarkably higher, reaching 6.7%, 12.3%, and 13.8%, respectively [5].

Cardiovascular complications, mainly myocardial ischemia, left ventricular dysfunction, and arrhythmia—occur in one in seven patients older than 45 years within 30 days from an inpatient non-cardiac surgery [6]. Similarly, pulmonary complications are common—particularly after major abdominal surgery—with an estimated incidence of 9 to 40%. Atelectasis, pneumonia, and pulmonary aspiration are among the most common postoperative complications and can impact survival after surgery. Preoperative medical assessment prior to every major surgery has become the standard of care with objectives to assess the perioperative risk for morbidity and mortality, optimize the patient's medical condition, and mitigate the risk for cardiopulmonary complications and others [9]. A number of validated risk stratification tools, such as the Revised Cardiac Risk Index (RCRI), American University of Beirut (AUB)-HAS2 Cardiovascular Risk Index, the American Society of Anesthesiologist's Physical Status (ASA-PS), and the Gupta perioperative risk for myocardial infarction and cardiac arrest have been created and used to standardize and optimize the perioperative medical assessment process [10–12]. The utilization of point of care ultrasound (POCUS)—the application of portable ultrasound by clinicians at the bedside—has grown rapidly in the inpatient and outpatient settings and is a valuable tool that enhances the standard clinical assessment [13]. In particular, lung POCUS can reveal findings, such as mild pulmonary edema, atelectasis, fibrosis, or small pleural effusions, which can be subclinical and otherwise not detected by history and physical examination alone [14]. A structured approach to performing and evaluating lung POCUS has been highly useful. This was originally known as the lung ultrasound score, and was later refined by Dell'Aquila et al. as the integrated lung ultrasound score (iLUS) [15,16].

Studies conducted in the immediate preoperative period have shown that lung POCUS performed during anesthesiology evaluation can aid in determining fluid therapy and predicting major adverse cardiac events [17,18]. However, the specific role of POCUS beyond this immediate preoperative assessment of patients has not been studied adequately, especially in the clinic setting at the time of preoperative medical assessment [19].

## Aims and Hypothesis

We aim to study the value of adjunctive iLUS at the time of preoperative medical assessment by internal medicine physicians on postoperative cardiopulmonary outcomes. Our primary hypothesis is that early lung POCUS assessment in moderate- to high-risk adult patients over 50-years-old undergoing abdominal surgery can reduce postoperative complications, thereby decreasing intensive care unit admissions, mortality, hospital length of stay, and readmissions.

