## Methods

### Study design and setting

This observational prospective pilot study will be conducted in New York City Health + Hospital (NYC H+H)/Jacobi, New York, United States of America affiliated to Albert Einstein College of Medicine and Laikon General Hospital, Athens, Greece affiliated to National and Kapodistrian University of Athens. The study has been reviewed and approved from Biomedical Research Alliance of New York (BRANY) and the respective NYC H+H committee, as well as the ethics committee of Laikon General Hospital. Verbal informed consent will be obtained from all participants. Written consent was waived as POCUS is the standard of care and an integral part of physical examination in modern clinical medicine.

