### Intervention

Included patients will undergo lung POCUS examination as part of their preoperative medical assessment prior to surgery. This is typically performed by an internal medicine specialist, and is usually done in a week to a few days in an outpatient clinic (in case of elective surgeries), and inpatient 0-1 days prior (in case of urgent surgeries). The studies will be performed by a sole operator (author LP), who was trained in POCUS during his internal medicine residency program, has attended POCUS courses via the American College of Physicians, and has been using POCUS on a daily basis in his clinical practice for more than five years. A single operator was chosen to eliminate the impact of inter-operator variability. POCUS images will be saved. To validate the findings, the operator's interpretation will be confirmed by an independent reviewer, who is a POCUS-trained critical care attending physician at NYC H+H/Jacobi (author PG). Clinicians will be blinded to lung POCUS findings, which is in-line with the high-quality POCUS literature [18]. Exceptions will include POCUS findings that are considered by the operator as critical, such as possible lung collapse, severe pulmonary edema, or large pericardial effusion, which will be reported to the clinicians.

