## Strengths

The study will explore an understudied topic on POCUS literature where research data is needed. This will be a real-world pragmatic study that will be conducted in two public hospitals in the Bronx, New York and in Athens, Greece, including patient populations that are typically underrepresented in research. All included patients will undergo lung POCUS by the same POCUS-trained clinician, and all images will be reviewed and validated by another POCUS-trained physician ensuring quality of acquired data. The lung POCUS protocol that will be used is one of the most comprehensive ones described in literature [15].

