## Conclusion

Our study will attempt to shed light on the role of lung POCUS in the preoperative clinic and its impact on patient outcomes, as well as to pave the way for more research on preoperative POCUS. While this will be a small pilot study, the results from the study can be used to inform the design of larger randomized controlled trials and subsequently affect guidelines on preoperative medicine.

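### The primary hypothesis is that scanning reduces complications, but the design scans everyone and can address only whether iLUS is associated with outcome

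*Protocol article*

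**What the plan says.** The Aims and Hypothesis section states as primary hypothesis that "early lung POCUS assessment in moderate- to high-risk adult patients over 50-years-old undergoing abdominal surgery can reduce postoperative complications", and expects fewer ICU admissions, fewer deaths, shorter stays and fewer readmissions to follow. The sentence before it is more neutral: it speaks of studying what iLUS adds at the preoperative assessment.

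The rest of the article describes a different study:

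- **Design** (Study design and setting): "This observational prospective pilot study will be conducted in" two hospitals. No allocation is described.
- **Exposure** (Intervention): "Included patients will undergo lung POCUS examination as part of their preoperative medical assessment prior to surgery". The Strengths section confirms it: "All included patients will undergo lung POCUS by the same POCUS-trained clinician".
- **Use of the result** (Intervention): "Clinicians will be blinded to lung POCUS findings". There is one carve-out: "Exceptions will include POCUS findings that are considered by the operator as critical".
- **Comparison** (Methodology of Analysis): patients are split by iLUS in three ways (zero or above zero, at the mean, at the median). A multivariate model contains the iLUS classification with RCRI, ASA-PS, AUB-HAS-2 and other covariates.
- **Critical findings**: extra tests or interventions before surgery in response to them are a secondary endpoint. The Methodology of Analysis adds a subgroup analysis of these patients and a sensitivity analysis without them.
- **Stated purpose elsewhere**: the Abstract says the study is "to evaluate the association of lung POCUS findings in the preoperative visit on the risk of adverse cardiopulmonary outcomes", and the Discussion gives the same associational purpose. The Conclusion speaks of "the role of lung POCUS in the preoperative clinic and its impact on patient outcomes".
- **Interim rule** (Methodology of Analysis): after 60 participants complete follow-up, enrolment ends if the findings decisively settle the study hypothesis either way.

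**The concern.** The hypothesis labelled primary is causal: doing the scan lowers the complication rate. Testing it needs patients who were not scanned, or comparable patients whose results were withheld in one group and disclosed in the other. The article describes neither. Blinding the clinicians suits a study of prognosis, but it also closes the route by which a scan could change care, except where a finding is judged critical.

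Two things are at stake. First, the article carries two incompatible objectives, and the one it calls primary is the one its data cannot answer. Second, an operational decision depends on it: enrolment may stop at the interim look on confirmation or rejection of the study hypothesis. If that means the hypothesis in Aims and Hypothesis, no result from this cohort can trigger the rule validly.

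**Working it through.** There is no stated figure to reproduce: the article gives 120 patients with no effect size, event rate or power attached. The check is whether the contrast that the hypothesis needs exists in the design.

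**Step 1. What the hypothesis needs.** A reduction due to scanning is a difference in risk between scanned and comparable unscanned patients, or between disclosed and withheld results among patients with comparable findings.

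**Step 2. What the design supplies.**

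| Contrast | Group 1 | Group 2 | Available? |
|---|---|---|---|
| Scanned vs not scanned | 120 planned | 120 − 120 = 0 | No |
| Disclosed vs withheld, comparable findings | Critical findings, disclosed | None: disclosure follows from the operator's judgement that the finding is critical | No |
| iLUS strata among the scanned | Lower iLUS | Higher iLUS | Yes |

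The first row has an empty group, and no historical or external control is described. A larger cohort would not help, because the second group would still be empty. The third row estimates whether iLUS goes with outcome among people who were all scanned. It says nothing about what would have happened to them without a scan.

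**Step 3. Whether the disclosed patients rescue the hypothesis.** They are the only patients in whom the scan can alter management. But disclosure is triggered by severity, so disclosed and undisclosed patients differ in the finding itself, and no patient with a similar finding has it withheld. The subgroup analysis is therefore uncontrolled. The sensitivity analysis that drops these patients shows how far the association depends on them. Neither estimates a reduction.

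**Step 4. Which stated aim fits.** The aim in the Abstract and Discussion, an association of findings with postoperative outcomes, matches the universal scanning, the blinding, the iLUS classifications and the multivariate model. The primary hypothesis matches none of them.

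**Step 5. The interim rule.** It refers to the study hypothesis. The only statement labelled as a hypothesis is the causal one, so as written the rule points to a claim that the data cannot confirm or reject.

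**The case against.** The strongest reply is that this is one badly worded sentence in an otherwise coherent prognostic study. The Abstract, Discussion and Limitations all speak of association, the blinding and analysis suit that aim, and the article calls itself a pilot that will inform randomised trials. Most of this stands, and it makes the correction cheap. It does not remove the need for one: the sentence is labelled primary, and the stopping rule refers to the hypothesis. Pilot status excuses imprecision, not an absent comparator. An unseen analysis plan could not supply a comparator that the design lacks.

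A second reply is that critical findings are disclosed and followed up, so the study does learn something about how scanning changes management. That is fair as description, but those data have no control.

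Several stronger readings are tempting and are not supported:

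- *The hypothesis and the analysis predict opposite directions.* The Methodology of Analysis states no expected direction for the iLUS comparisons. More events with higher iLUS is a plausible expectation, but it is an inference.
- *The scan cannot affect care in most patients.* The article gives no frequency of critical findings, so the share of patients is unknown.
- *A positive association will be reported as benefit.* The Conclusion's wording is loose, but the same section defers to larger randomised trials. This supports a wording correction only.
- *There is a randomised comparison after all.* The Methodology of Analysis mentions intention to treat and preserving randomisation, but the study is observational and describes no allocation. That wording cannot be read as a control group.

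**Conclusion.** The point holds as a contradiction between the stated primary hypothesis and the stated design. Information on a reduction due to scanning is nil (120 scanned, 0 unscanned), whatever the event rate. The prognostic association remains estimable, so a reader should not infer that the study as a whole is without value: the data collection fits the aim in the Abstract and Discussion.

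The conclusion rests on two readings of the text: that every included patient is scanned, which the article says in two places, and that no control group exists beyond what is described. It does not depend on how often critical findings occur, because the disclosed patients are uncontrolled at any frequency. It should be corrected before the interim look, since the decision to stop enrolment refers to this hypothesis.

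**What to change.** 1. In Aims and Hypothesis, restate the primary hypothesis as an association between preoperative iLUS and the 30-day primary composite, including after adjustment for RCRI, ASA-PS and AUB-HAS-2 in the multivariate model already planned.
2. In Methodology of Analysis, tie the interim rule to that restated hypothesis, and align the wording on randomisation with an observational cohort.
3. In the Conclusion, replace the phrase about impact on outcomes with association wording, and leave the causal question to the later randomised trials foreseen there.

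The cost is a change of wording. No extra patients, procedures or analyses are needed.

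A specific measure of added value, such as a likelihood-ratio test or a change in c-statistic, is optional and not part of the correction. It could be very imprecise here. The article gives no rate for the composite. If, as an assumption only, the 30-day morbidity rates in the Introduction applied, 120 patients would give 120 × 0.067 ≈ 8 to 120 × 0.138 ≈ 17 events. At the pulmonary complication range quoted there, the figures would be 120 × 0.09 ≈ 11 to 120 × 0.40 = 48.
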